## Abstract

**Background:**

Globally, household air pollution (HAP) is a leading environmental cause of morbidity and mortality. Our trial aims to assess the impact of liquefied petroleum gas (LPG) for cooking to reduce household air pollution exposure on child health outcomes, compared to usual cooking practices in Bangladesh. The primary aim is to evaluate if reduced exposure to HAP through the provision of LPG for cooking from early gestation through to age 2 improves child anthropometry, health, and neuro-cognitive developmental outcomes, compared to children exposed to emissions from usual practice.

**Methods:**

Two-arm parallel cluster randomized controlled trial (cCRT). We will extend the intervention and follow-up of our existing “Poriborton” trial. In a subset of the original surviving participants, we will supply LPG cylinders and LPG stoves (intervention) compared to usual cooking practices and extend the follow-up to 24 months of age. The expected final sample size, for both (intervention and control) is 1854 children with follow-up to 2 years of age available for analysis.

**Discussion:**

This trial will answer important research gaps related to HAP and child health and neuro-cognitive developmental outcomes. This evidence will help to understand the impact of a HAP intervention on child health to inform policies for the adoption of clean fuel in Bangladesh and other similar settings.

**Trial registration:**

The Poriborton: Change trial: Household Air Pollution and Perinatal and early Neonatal mortality is registered with the Australian New Zealand Clinical Trials Registry, ACTRN12618001214224, original trial registered on 19th July 2018, extension approved on 23rd June 2021. www.anzctr.org.au.

## Administrative information

Note: the numbers in curly brackets in this protocol refer to SPIRIT checklist item numbers [1]. The order of the items has been modified to group similar items (see http://www.equator-network.org/reporting-guidelines/spirit-2013-statement-defining-standard-protocol-items-for-clinical-trials/).

## Introduction

### Background and rationale {6a}

Globally, household air pollution (HAP) is one of the leading environmental causes of death and adverse health outcomes [2]. HAP consists of emissions from burning solid fuels for cooking or heating that contain toxic respirable particles, including particulate matter (PM2.5, < 2.5 μm in diameter, and PM10 < 10 μm) [3]. Approximately 3.8 billion people or 49% of the world’s population, mostly poor people from low- and middle-income countries (LMIC), are still exposed to HAP from the use of solid fuels for cooking and heating, contributing to over 4 million premature deaths [2, 4]. Measurement of PM2.5 in households using solid fuels is at least 10 to 50 times in excess of the safe levels set by the WHO. Women and children are particularly at risk due to a combination of their higher vulnerability and chronic levels of exposure due to the gendered division of labor and domestic responsibilities [5]. The use of inefficient stoves in poorly ventilated areas and long hours cooking and heating cause exposure to HAP [3]. Children under the age of five are more likely to be exposed to HAP, staying close to their mothers near the domestic hearth.

Over 149 million children under five suffered from stunting in 2020 [6], and HAP is considered to account for a large proportion of stunting [7, 8]. Stunting is defined as height-for-age 2 standard deviations below the growth standards, and stunted children have both physical and cognitive developmental delays. Few studies examine the biological pathways by which HAP causes stunting [9]. It may be through the same pathway that exposure to environmental tobacco smoke reduces birth weight, thus contributing to stunting [10, 11], or through acute respiratory infections [12], or anemia [13], all of which are associated with stunting. During the antenatal period, exposure to air pollution may induce oxidative stress or systematic inflammation that occurs, as a result, may be a pathway to growth retardation [9]. Exposure to air pollution during the postnatal period may promote stunting via impairments in the immune system and development, clinical and subclinical infections, changes in nutrition (dietary intake and metabolism), and altered bone metabolism [9]. The epidemiological evidence is from retrospective observational studies. A recent review of solid fuel use on stunting ascertained that those children living in homes that used solid fuels as the primary fuel source were three times more likely to be severely stunted compared to those in households using cleaner fuel, such as liquefied petroleum gas (LPG) [12]. In a population-based study in India, children exposed to solid fuel compared to those unexposed had differences in mean height-for-age *z*-scores of 0.61, a 21.3% difference after accounting for confounding [14]. Further research from India revealed households using clean cooking fuels had reduced the likelihood of stunting after controlling for socioeconomic and demographic factors [8]. However, there have been no randomized controlled trials of HAP interventions and stunting, which this study aims to address.

HAP is a recognized lung health hazard, and early life exposure determines the lung function trajectory [15, 16]. The underlying cause of many acute lower respiratory infections (ALRI) deaths in children may be due to immature respiratory and immune systems and exposure to inefficient burning of solid fuels in households [5, 17–19]. Infants exposed to HAP experience ALRI’s in early life and are associated with reduced lung function and the persistence of respiratory symptoms [20]. Children living in households using solid fuel for cooking are far more as likely to develop ALRI compared to children in households using clean fuels [17, 21]. This suggests that early intervention is critical to improve lung health.

Evidence of the effect on child development and specifically on neuro-developmental delays from ambient air pollution literature has been accumulating [10–12, 22]. In a review of air pollution and cognitive outcomes, four included studies examined in utero exposure and follow-up ≤ 5 years of age, and eight studies examined postnatal exposure [14]. Pollution resulted in delays in motor, language and social skills at ages 6 and 18 months, and the postnatal exposure studies found effects mostly in boys. The studies were heterogeneous (design, population, source/type of exposure, follow-up), and all were observational. PM2.5 was specifically implicated in children aged 15 months; with every 1 μg/m3 increase in PM2.5, there were significant decreases in the mental score of the Bayley Scales of Infant Development (*β* = − 0.39 with PM2.5 exposure) [23].

To our knowledge, Poriborton is the largest trial specifically investigating reduced exposure to HAP and perinatal outcomes. This extension of Poriborton will make it one of the longest intervention and follow-up periods of the trials in this field. It specifically addresses identified research priorities related to HAP, including investigating the risk of severe infection, child growth, and cognitive development [8]. This trial will help to understand the impact of a HAP intervention on child health using existing research infrastructure and produce high-quality evidence.

### Objectives {7}

The primary aim is to evaluate if reduced exposure to HAP through the provision of LPG for cooking from early gestation through to age 2 improves child growth, respiratory illness, and neuro-cognitive developmental outcomes. Specifically, we aim to evaluate if reduced exposure to HAP to age 2 reduces stunting by 20% (28% in intervention and 35% control), significantly reduces the prevalence and severity of acute lower respiratory infections, improves child development by 0.3 SD at 24 months of age, and is a cost-effective intervention to deliver to the community considering the return to investment.

### Trial design {8}

The study design is a two-arm cluster randomized controlled superiority trial (cRCT). We will use the existing trial infrastructure of Poriborton trial, which provided LPG cylinders and LPG stoves from early pregnancy until birth, and the control arm continued usual cooking practices. The usual cooking practice in this setting is a traditional clay stove with various biomass fuels. For further details, see the Poriborton trial protocol [24]. We will use the existing trial infrastructure of Poriborton and seamlessly continue the LPG cylinder provision (intervention), extending the follow-up to 24 months of child’s age in the intervention arm. The intervention of the extension will commence around the time of birth (once the most recent cylinder needs replacing but not before seven completed days post-partum), and hence, we will have uninterrupted LPG coverage up to 2 years of age.

## Methods: participants, interventions, and outcomes

### Study setting {9}

The study will be conducted in the Sherpur District of Mymensingh Division, Bangladesh (Fig. 1, authors own map). The Sherpur district is located approximately 200 km north of Dhaka and has been chosen based on the high neonatal mortality rates and the low saturation of the use of LPG fuel for cooking [25]. Sherpur has a population of ~ 1,170,219 living in rural areas that are divided into five sub-districts. Of these five sub-districts, we have purposively selected two for the study based on the road conditions that allow a good vehicular access with the district headquarters for the transportation of LPG cylinders as well as field team access.

**Fig. 1 Fig1:**
[figure not shown]
Sherpur, the Poriborton study site, in Northern Bangladesh, divided by Unions (main picture). Insert: Bangladesh divided by Districts, and the selected Sub-Districts (red)

### Eligibility criteria {10}

The Poriborton-Extension Trial has two levels of inclusion and exclusion criteria. Inclusion criteria for this extension part of the trial were mother-child dyads from the Poriborton trial cohort who gave birth to a liveborn infant and who was still alive on or after 15 June 2021 and who gave consent and were willing to continue to participate in the study up to 24 months of the child’s age. Exclusion criteria are women who had a pregnancy loss or stillbirth, the child died before the 15th of June or a livebirth, but the child died before the enrollment visit was made. In case of multiple live births from a pregnancy, all children will be enrolled if they meet the inclusion and exclusion criteria.

### Who will take informed consent? {26a}

Poriborton evaluation staff will recruit mother-child dyads from the original Poriborton trial and obtain informed consent from June 2021.

### Additional consent provisions for collection and use of participant data and biological specimens {26b}

N/A as we do not collect biological specimens for storage.

### Interventions

#### Explanation for the choice of comparators {6b}

The LPG arm will be compared to the control arm (usual cooking practice), to evaluate if reduced exposure to HAP through provision of LPG for cooking from early gestation through to age 2 improves child anthropometry, health, and neuro-cognitive developmental outcomes

#### Intervention description {11a}

The LPG fuel intervention for this extension will commence around birth when the previous cylinder is almost empty. Gas replenishment will continue free of cost until the infant is 24 months old. We have an existing LPG fuel distribution system in operation built into our electronic data collection system. We will continue with the same distribution process with this application. A national gas distribution company will supply the LPG with Bangladesh Standards and Testing Institution certification for cylinder quality. Based on the average duration of use of a cylinder by an average-sized household, we will require approximately 24 refills for each participant until the child is 24 months of age.

The intervention is distributed at the individual level but randomized at the cluster level to reduce community tensions and overall exposure and leverage community-level adoption of clean cooking. We will conduct outcome assessments at the individual level. Allocation concealment is impractical due to the cluster design and nature of the intervention. Participants and their households receive the intervention based on their cluster of residence (Fig. 2).

**Fig. 2 Fig2:**
[figure not shown]
Flow diagram of Poriborton and Poriborton-Extension

Our field implementation team is trained in technical issues for gas stove installation, troubleshooting and maintenance, and cylinder replacement. They will continue to provide support to intervention households who require external assistance as necessary. These stoves will adhere to the Bangladesh Standards and Testing Institution requirements. We will replace the stoves in case of mechanical faults during the 2 years of use. Control women will continue with usual cooking practices (mostly traditional cooking) and will be followed up for outcome evaluation up to 24 months of child’s age. Participants from the control arm will be provided 200 Taka as time compensation during the six visits (3, 6, 12, 18, 24 months of child’s age).

#### Criteria for discontinuing or modifying allocated interventions {11b}

The icddr,b’s ethics review committee requires reporting of all serious adverse events within 24 h; for this study, all adverse events will also be reported by the study investigators within 24 h of their occurrences using a standard case reporting form. We anticipate minimal risk to the participants from the study interventions. The quality of gas and stoves are ensured according to the Bangladesh Standards and Testing Institution standards. To avoid rare accident events from LPG stove, extensive counseling and guidance on safety precautions are provided to intervention participants before installing the stove and every 2 months throughout the intervention.

#### Strategies to improve adherence to interventions {11c}

The field implementation team will conduct regular visits (every 2 months) to support intervention households and answer any queries as needed. Based on extensive formative research, we have developed behavior change communication materials that encourage, promote, and support the safe, proper, and consistent use of LPG for cooking. The materials include calendars, leaflets, and short videos.

#### Relevant concomitant care permitted or prohibited during the trial {11d}

N/A as there are no relevant interventions prohibited.

#### Provisions for post-trial care {30}

If the results are favorable to the intervention, we will work with relevant stakeholders to ensure access to the intervention for all communities; these discussions have already commenced.

#### Outcomes {12}

The primary outcome for this trial will be the proportion of stunted children (height-for-age < − 2 Z) at 24 months in the intervention arm compared to the control arm.

Secondary outcomes include the following: (i) mean height-for-age *Z* scores, (ii) mean weight-for-length *Z* scores and prevalence of wasting (weight-for-length < − 2 Z) in children, (iii) mean absolute height-for-age differences, health outcomes: (iv) number of events and mean days with diarrhea, acute respiratory illness and fever, at 6, 12, 18, and 24 months of child’s age, (v) differences in Bayley Scales scores in cognitive, motor and language domains, and Wolke’s behavior ratings during Bayley test (vi) differences in household income/expenditure, (vii) cost of delivering the intervention and costs of upscaling, and (viii) cost-effectiveness of the intervention compared to usual cooking providing estimates of the incremental cost per stunted child prevented and incremental cost per disability-adjusted life years averted, (ix). Intermediate outcomes include PM2.5, 24-h averaged mean, and any differences in gender roles (self-efficacy, time use).

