#### Sample size {14}

We expect the final sample size to be at least 1854 children (927 in each arm) with follow-up up to 24 months of child’s age available for analysis. This assumes ten per cent loss-to-follow-up due to mortality in the first 2 years of age (3%), migration out (3%), and withdrawals (2%). For this sample size, we have at least 88% power to detect a 20% lower risk (relative risk =0.8) in stunting, assuming 35% stunting in the control vs 28% in the intervention, an intraclass cluster correlation of 0.02, which is based on the previous cRCT on stunting, [26] and a two-sided significance level of 0.05. If the intraclass correlation is twice as large, i.e., intraclass correlation 0.04, [25], we would still have 80% power. For the secondary outcomes, the final sample size will provide at least 80% power to detect moderate effect sizes for many, if not all, secondary outcomes. For example, we will have 90% power to detect a standardized difference of 0.2 between arms for height-for-age *z*-score. Any differences in perinatal outcomes from Poriborton will not impact the integrity of the extension. We expect reduced perinatal mortality and higher birth weights. Additional live births will result in a slightly higher sample size in the intervention arm for the extension. We investigated this scenario in our power calculation and found the differences in cluster size will remain relatively small and less likely to impact the power.

For the personal exposure of household air pollution, a sample size of 120 children from each arm will be used to estimate reductions in PM2.5. This sample size will allow us to detect a 28% difference (50% and 70% in intervention and control, respectively) (WHO target [3]) with > 80% power.

The expected number of live births (> 7 days old) eligible is 2154, corresponding to all women enrolled in Poriborton from October 2020, of which we expect 10% fetal loss and up to 5% lost-to-follow-up due to migration (3%) or withdrawal (2%). Of the 2154 births (infants), we expect 2060 to be enrolled into the Poriborton-Extension, conservatively assuming that 4% of the newborns die prior to enrollment or decline to participate in the extension.

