##### Child anthropometry

Trained research assistants will collect anthropometric data (weight and height measurements) using in-field electronic data capture on tablets and established methods [27], which will be standardized before and during data collection. Anthropometry will be collected at 6, 12, 18, and 24 months of child’s age. We will use the WHO Growth Standard [28] to construct anthropometric indices and standard indicators, including stunting (height-for-age < − 2 Z), wasting (weight-for-height < − 2 Z), and underweight (weight-for-age < − 2 Z). Children with very low weight-for-height (Z < − 3) will be referred for assessment and treatment for severe acute malnutrition and retained in the study.

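### The 90% power for height-for-age Z and the 88% for stunting do not follow from the inputs in the sample size section, which give about 93–98% and about 85%

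*Protocol article*

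**What the plan says.** All power statements are in the protocol article, Sample size {14}. The analysed number is given as "We expect the final sample size to be at least 1854 children (927 in each arm"), after attrition: "This assumes ten per cent loss-to-follow-up". Before those losses, "we expect 2060 to be enrolled into the Poriborton-Extension", which is 1030 per arm.

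For the primary outcome the section claims at least 88% power, "assuming 35% stunting in the control vs 28% in the intervention", with an ICC of 0.02 taken from an earlier cluster trial on stunting and a two-sided 0.05 level. It adds that power would still be 80% if the ICC were 0.04. As an example for the secondary outcomes, it says "we will have 90% power to detect a standardized difference of 0.2 between arms for height-for-age" Z-score. No separate ICC is given for that outcome.

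Sequence generation {16a} gives 103 clusters per arm. Outcomes {12} says "The primary outcome for this trial will be the proportion of stunted children" at 24 months and continues: "Secondary outcomes include the following: (i) mean height-for-age" Z-scores.

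**The concern.** A reader should be able to recover the stated powers from the stated inputs, and two of the three cannot be recovered. The HAZ figure is lower than the inputs give, and the primary figure at ICC 0.02 is higher.

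This affects how the results will be read. A non-significant stunting result would be judged against a power of 88% when the analysed number supports about 85%. A non-significant HAZ result would be judged against 90% when the inputs imply 93–98%, so it would be stronger evidence against a 0.2 SD difference than the protocol suggests. If a larger HAZ ICC or marked variation in cluster size lies behind the 90%, that is information a reader needs and cannot see.

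**Working it through.** **Inputs.** From Sample size {14}: 927 per arm analysed, 1030 per arm enrolled, 35% vs 28% stunting, ICC (ρ) 0.02 or 0.04, two-sided 0.05, HAZ difference 0.2 SD. From Sequence generation {16a}: 103 clusters per arm, so m = 927/103 = 9 children per cluster. Assumptions: all clusters contribute and, unless stated otherwise, they are of equal size.

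**Design effect.** DE = 1 + (m − 1)ρ.
- ρ = 0.02: DE = 1.16, effective n per arm = 927/1.16 = 799.1.
- ρ = 0.04: DE = 1.32, effective n per arm = 927/1.32 = 702.3.

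**Step 1: stunting.** Power = Φ{[0.07 − 1.96·√(2·0.315·0.685/n)] / √[(0.35·0.65 + 0.28·0.72)/n]}.
- ρ = 0.02: (0.07 − 1.96 × 0.02324)/0.02317 = 1.055, so 85.4%. Other two-sided versions (unpooled, arcsine, log odds ratio, t with 204 df, continuity-corrected) give 84.2–85.6%. The stated 88% is not reached.
- ρ = 0.04: 80.7%. The stated 80% reproduces.
- 1030 per arm (m = 10), ρ = 0.02: DE = 1.18, n = 872.9, power 88.3%. This matches the stated 88%, but it is the number before the 10% loss (2060 × 0.9 = 1854). With 1030 per arm and ρ = 0.04, power would be 83.5%.
- At 927 per arm, 88% would need an ICC of about 0.009, below the stated 0.02.

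**Step 2: HAZ, 0.2 SD, stated ICCs.** Power = Φ[0.2/√(2/n) − 1.96].
- ρ = 0.02: 0.2/0.0500 − 1.96 = 2.04, so 97.9%.
- ρ = 0.04: 0.2/0.0534 − 1.96 = 1.79, so 96.3%.

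**Step 3: HAZ, ICCs converted.** The 0.02 comes from a trial on stunting, so it may be a binary-scale value. The approximate continuous-scale ICC is ρ·p(1 − p)/φ(z)², with p = 0.315 and φ(z) = 0.355. The factor is 0.2158/0.1262 = 1.71, giving 0.034 and 0.068.
- 0.034: DE = 1.274, n = 728, power 96.8%.
- 0.068: DE = 1.547, n = 599, power 93.3%.

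**Step 4: what would give 90%.**
- Required effective n = 2(1.96 + 1.282)²/0.2² = 525.4. So DE = 927/525.4 = 1.764 and ICC = 0.764/8 = 0.096, more than twice the largest stated ICC.
- With unequal clusters, DE = 1 + [(1 + CV²)m − 1]ρ. Taking ρ = 0.068 and CV = 0.6 (an assumption), DE = 1.77 and power is about 90%. The same CV at stunting ICC 0.04 gives DE = 1.45 and stunting power of about 77%, which no longer matches the stated 80%.
- If 0.2 meant raw Z units with an SD of 1.2 (an assumption), power would be 91.5% or 87.8%, but the text says the difference is standardized.

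| Outcome | Stated | ICC 0.02 | ICC 0.04 |
|---|---|---|---|
| Stunting, 35% vs 28% | ≥88% (0.02); 80% (0.04) | 85.4% | 80.7% |
| HAZ 0.2 SD, ICC as stated | 90% | 97.9% | 96.3% |
| HAZ 0.2 SD, ICC converted | 90% | 96.8% | 93.3% |

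**The case against.** The strongest reply on HAZ is that the protocol never gives an HAZ ICC. The authors may have used a larger one, allowed for unequal clusters, or rounded down for safety. The 90% is then not proved wrong; it is only not derivable from what is printed. It is also cautious, illustrates one secondary outcome, and drives no sample size or decision. All of that stands and is why the point is minor. It does not remove the need to state the input that gives 90%. The stunting figure has no such defence, because its ICC and analysed number are both stated.

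A reader might go further and infer that mean HAZ should replace stunting as the primary outcome, or be tested ahead of it. The arithmetic is tempting. Under a normal shift, 35% vs 28% equals a difference of z(0.35) − z(0.28) = −0.385 + 0.583 = 0.198 SD, almost the 0.2 SD example, and the continuous test has more power for it. The documents do not support that step. Objectives {7} sets a reduction in stunting as the aim, and Outcomes {12} costs the intervention per stunted child prevented. The power advantage also rests on the whole HAZ distribution shifting equally, which the protocol neither states nor supports with data. Its background cites both a mean HAZ difference and an association with severe stunting.

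A simulation shows how much depends on this: 103 clusters of 9 per arm, continuous-scale ICC 0.034 or 0.068, 6,000 trials each. If the same 35% to 28% effect comes only from children below the median, HAZ power falls to about 51% or 43% while stunting keeps about 85% or 81%. Testing HAZ first would then cut the chance of a stunting claim to about 50% or 42%. Under a uniform shift the loss would be only 0.5 to 1 point. The shift patterns are assumptions.

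**Conclusion.** Two stated powers do not follow from the section's inputs. HAZ power for 0.2 SD is about 97–98% at ICC 0.02 and 93–96% at ICC 0.04, against a stated 90%. Stunting power at ICC 0.02 is about 85%, against a stated minimum of 88%, and the higher figure fits the enrolled rather than the analysed number. The 80% at ICC 0.04 is sound.

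This rests on 9 children in each of 103 clusters per arm, normal-theory formulas and, for the lower HAZ values, an approximate ICC conversion. Unequal clusters would lower all the powers somewhat: with a CV of 0.5 (an assumption), stunting at ICC 0.02 falls to about 84%.

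The point is minor. It does not show that the trial is underpowered, since stunting power stays near 81% at ICC 0.04 under these assumptions. It does not show that the primary test is invalid, and it gives no ground for changing the order of the outcomes.

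**What to change.** In Sample size {14}, or in the analysis plan and results paper if the article cannot be corrected:

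- Restate HAZ power for 0.2 SD as about 97–98% at ICC 0.02 and 93–96% at ICC 0.04, or keep 90% and state the HAZ ICC and cluster-size variation that produce it.
- Restate stunting power as about 85% at ICC 0.02 and about 81% at ICC 0.04 for 927 per arm. If 88% is kept, say that it refers to the 1030 per arm enrolled before losses.
- Say whether the ICCs of 0.02 and 0.04 are on the binary or the continuous scale.
- Leave stunting as the primary outcome and mean HAZ as secondary outcome (i).

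The cost is a few sentences. No children, visits, measurements or analyses change.
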